## Abstract

**Background:**

Vascular cognitive impairment with no dementia (VCIND), manifested mainly as mild impairment of concentration and executive function, is the early phase of vascular dementia (VD). Currently, there is no specific treatment for VCIND. We hypothesize that electrical acupuncture can improve the mental and motor functions of patients with VCIND. Thus, we designed this randomized controlled trial to test this hypothesis by comparing the therapeutic effect of electrical acupuncture versus sham acupuncture in patients with VCIND.

**Method/Design:**

In this single-center 3-year study, 120 eligible patients will be recruited and randomly assigned to receive electrical acupuncture treatment (n = 60) or sham acupuncture (n = 60) for 8 consecutive weeks (24 sessions in total), with the same acupoint prescription (DU20, EX-HN3, DU24, DU17, DU26, EX-HN1, HT7, PC6, GB20, SP6). The primary assessment is the Montreal Cognitive Assessment. The secondary assessments are the Modified Barthel Index and Event-Related Potential. All outcomes will be assessed at baseline, endpoint, and follow-up at 8 and 24 weeks after the end of treatment.

**Discussion:**

If the outcome confirms the effectiveness and safety of electrical acupuncture in treating VCIND, this treatment is expected to be promoted in clinical practice to treat such patients.

**Trial Registration:**

Chinese Clinical Trial Registry identifier: ChiCTR-IIR-17011513; Registered on 27 May 2017.

**Electronic supplementary material:**

The online version of this article (10.1186/s13063-018-2458-1) contains supplementary material, which is available to authorized users.

## Background

Although global stroke incidence and mortality declined from 1999 to 2013, the absolute number of people affected by stroke continues to increase rapidly [1], with up to 41% of them suffering from varying degrees of cognitive impairment in the first year after the stroke [2], with ischemic stroke likely facilitating the onset of dementia [3]. Deb et al. [4] studied the costs of caring for people with dementia, finding that it has been a great social burden in the United States from 2006 until 2017. Among all types of dementia, vascular dementia (VD) is the second most common type after Alzheimer’s disease (AD), accounting for 10% to 50% of the entire demented population [5].

Vascular cognitive impairment with no dementia (VCIND) is the early phase of VD, and manifests mainly as impairment of concentration and executive function [6, 7]. The presence of VCIND means that the patient’s current cognitive function has been impaired and implies further deterioration. However, with timely diagnosis and following effective treatment, the progression of VCIND, and even its development into VD, can be delayed. Furthermore, cognitive function is one of the essential factors that influence the prognosis of stroke rehabilitation. Thus, together with the activities of daily living, improving cognitive function is very important in the overall rehabilitation process for stroke patients [8].

Electrical acupuncture therapy coordinates the balance of yin and yang, and regulates the organs’ functions and mental status [9]. In fact, previous research on electrical acupuncture treating mental diseases have revealed its advantages, including relieving symptoms, reducing adverse reactions to long-term medication, and improving their curative effect, as well as delaying the progression of disease [10, 11]. There are studies that support the therapeutic effect of electrical acupuncture therapy on alleviating the severity of cognitive impairment and improving the quality of life of patients [12, 13]; however, most of these studies are empirical [14]. The deficit of objectivity makes the findings of those reports far from persuasive and thus limits the common application of acupuncture for VCIND. Therefore, through this proposed randomized controlled trial (RCT), we intend to obtain better evidence for the use of electrical acupuncture in the treatment of VCIND.

## Methods and design

### Hypothesis

Participants with VCIND who receive electrical acupuncture treatment will have an improvement in their mental and motor functions.

### Objectives

To compare the difference in improvement of cognitive function and mental states, assessed by the Montreal Cognitive Assessment (MoCA), between the intervention group and control group.To compare the difference in improvement of daily-life ability, measured by the Modified Barthel Index (MBI), between the intervention group and control group.To compare the difference in improvement of Event-Related Potential (ERP) abnormality between the intervention group and control group.

### Design

We developed this single-center, single blind RCT according to the Standard Protocol Items: Recommendations for Interventional Trials Statement. The participant flowchart can be found in Fig. 1 and details of study process and data collection will be elaborated in Fig. 2 and Additional file 1.

**Fig. 1 Fig1:**
[figure not shown]
Study process. Shows the flowchart of patients through the study process

**Fig. 2 Fig2:**
[figure not shown]
Standard Protocol Items: Recommendations for Interventional Trials Statement (SPIRIT) Figure. Shows the enrolment, interventions, and data collection

### Methods

Ethical approval has been obtained from the ethics committee of Shanghai Municipal Hospital of Traditional Chinese Medicine affiliated with Shanghai Traditional Chinese Medicine University in March 2017.

A recruitment notice directed to post-stroke patients with cognitive impairment and their companions will be posted on an official information platform or bulletin boards at Shanghai Municipal Hospital of Traditional Chinese Medicine in Shanghai, China. Any interested patients, both as in-patients or out-patients, can reach the researchers through the phone number provided. After being informed of the details of this RCT, voluntary participants will be evaluated by experts in the neurological department of this hospital, and those that meet the selection criteria will be asked to sign the informed consent (Additional file 2) before being accepted into this RCT.

#### Inclusion criteria

Patients aged 45–80 years who (1) complain of or are reported by a relative or accompanying person as having cognitive decline; (2) have imaging evidence that supports cerebrovascular disease, and may or may not have a medical history of transient ischemic attack or other types of stroke; (3) have symptoms or signs caused by cerebrovascular disease (e.g., hemiplegia, hemiparesis, problems with understanding or forming speech, numbness or strange sensations); and (4) obtain the following results in the neuropsychological assessment under professional instruction from the neurologist: MoCA score < 26; clinical dementia rating scale score = 0.5; modified Rankin scale score ≤ 3; Hachinski ischemic score > 7 points, will be included in the study.

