#### Exclusion criteria

Patients who (1) have a Mini-mental State Examination score < 21; (2) have co-morbidity including AD, Parkinson’s disease, frontotemporal dementia, or Huntington’s disease, central nervous system inflammatory demyelinating disease, epilepsy, psychosis, liver or kidney dysfunction, hypothyroidism, alcoholic or drug abuse related encephalopathy, depression; and (3) have severe visual impairment, hearing impairment, severe aphasia or limb dysfunction which might affect pre-assessment, will be excluded from the study.

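### Time since the last stroke or TIA is left open, and the stated t test on MoCA change leaves any resulting variance unadjusted

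*Protocol article*

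**What the plan says.** Under Inclusion criteria, the protocol article requires that patients "have imaging evidence that supports cerebrovascular disease, and may or may not have a medical history of transient ischemic attack or other types of stroke" and that they "have symptoms or signs caused by cerebrovascular disease". The scale limits are "MoCA score < 26; clinical dementia rating scale score = 0.5; modified Rankin scale score ≤ 3; Hachinski ischemic score > 7 points". The Exclusion criteria remove patients who "have a Mini-mental State Examination score < 21", those with listed co-morbidities, and those with severe sensory, speech or limb problems that could disturb the pre-assessment. All of these limits describe severity or cause at the time of screening. None concerns when the last event happened or whether the deficit is stable.

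Under Methods, recruitment is by "A recruitment notice directed to post-stroke patients with cognitive impairment and their companions", and it continues: "Any interested patients, both as in-patients or out-patients, can reach the researchers through the phone number provided".

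The primary outcome is change in MoCA, first reassessed 8 weeks after treatment starts. The article describes a 1:1 random list without naming a stratification factor. Under Data analysis it names Student's t test for measurement data, without a covariate.

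**The concern.** Two patients with the same MoCA score at screening, one shortly after a stroke and one years after, can both qualify. The first may improve over 8 weeks without effective treatment, and the second may not. The primary outcome is change over exactly that period, so a mixture of the two natural courses widens the spread of MoCA change in both arms. An unadjusted two-sample test treats that spread as noise. At stake is some power, together with the reader's ability to see to whom the result applies if time since the event is not recorded.

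**Working it through.** The plan gives no figure on this point to reproduce. It states no SD of MoCA change, no expected natural recovery and no expected share of recent cases. Its sample size is built on rates, with no stated power. What follows is an illustration over a range.

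**Input from the protocol article:** 50 evaluable patients per arm; two-sided 5% level.

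**Assumptions:** SD of MoCA change 3 within each class (recent; chronic or no event); share of recent cases f = 0.2 to 0.5; extra natural gain in recent cases g = 1 to 3 points over 8 weeks; the same treatment effect in both classes; 80% power at 50 per arm if all patients followed one natural course.

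**Step 1, difference detectable with 80% power:** δ = (1.960 + 0.842) × 3 × √(2/50) = 2.802 × 3 × 0.2 = 1.68 points.

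**Step 2, variance of change in the mixed population:** 9 + f(1 − f)g².

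**Step 3, power of the unadjusted comparison (normal approximation):** Φ(δ / (SD × √(2/50)) − 1.960).

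| f | g | Variance | Ratio to 9 | SD | Power |
|---|---|---|---|---|---|
| 0.2 | 1 | 9.16 | 1.02 | 3.03 | 0.793 |
| 0.2 | 2 | 9.64 | 1.07 | 3.10 | 0.772 |
| 0.2 | 3 | 10.44 | 1.16 | 3.23 | 0.739 |
| 0.5 | 1 | 9.25 | 1.03 | 3.04 | 0.789 |
| 0.5 | 2 | 10.00 | 1.11 | 3.16 | 0.757 |
| 0.5 | 3 | 11.25 | 1.25 | 3.35 | 0.707 |

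To keep 80% power, the size per arm would rise in proportion to the variance, from 50 to between 51 (50 × 1.02) and 63 (50 × 1.25). If the within-class SD is allowed to run from 2.5 to 4, power lies between about 0.80 and 0.67, and the size needed between 51 and 68 per arm.

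**Step 4, chance imbalance:** imbalance between arms in the share of recent cases moves the arm difference with an SD of g√(2f(1 − f)/50), which is 0.08 points at f = 0.2, g = 1 and 0.30 points at f = 0.5, g = 3. This is already counted in step 3. At f = 0.5, g = 3 the variance of the arm difference is 2 × 11.25/50 = 0.45. Of that, 2 × 9/50 = 0.36 is within-class variance, and the remaining 0.09 = 0.30² is the imbalance.

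**Step 5, bias:** under randomisation the expected share of recent cases is the same in both arms. The expected natural gain, f × g (0.2 to 1.5 points under these assumptions), is therefore also the same and cancels from the difference.

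**The case against.** A reader might infer more than the documents support.

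- **A contradiction with the Background.** The Background says of vascular cognitive impairment with no dementia that it "implies further deterioration". That is a general prognosis and not an eligibility condition. The same section opens with impairment in the first year after stroke and speaks of stroke rehabilitation. The Hypothesis expects improvement and does not describe the condition as persistent or progressive. There is no contradiction.
- **A bias.** The objective is the difference in improvement between two concurrent randomised arms, so natural recovery cancels in expectation. The t test also remains valid, because the extra spread enters its standard error. Only precision is lost.
- **That recent cases will be enrolled, or that much of any gain will be natural recovery.** In-patient status is not the same as a recent stroke, a stroke history is optional, and the severity limits may keep some early cases out. The share of recent cases is unknown, and the documents give no expected total gain for comparison.
- **That a minimum interval is needed.** The Discussion explains that a broad, early population was chosen for the sake of generalisability. It does not mention time since stroke, but narrowing entry would trade that aim, and some recruitment, for homogeneity.

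It can also fairly be said that an article commonly leaves stratification factors, covariates and baseline items to fuller documents, which are not shown. Their absence here is therefore not a defect in itself, and if those documents already handle time since the event, the point is met. What stands is that the criteria, given in detail, admit both kinds of patient, and that the comparison named for measurement data is an unadjusted t test.

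**Conclusion.** The point holds as one of precision and description. The criteria let recently affected and chronic patients enter together, and the stated analysis leaves any difference in their natural MoCA change in the error term. The loss ranges from under 1 percentage point of power to about 9 (79% down to 71%, from 80%) at an SD of 3. The upper end needs half the sample to be recent cases and a 3-point extra gain together. These figures rest wholly on the assumed SD, share, gain and starting power, because the documents supply none of them. Variance and chance imbalance are one loss and must not be added. The sham-controlled comparison stays unbiased.

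**What to change.** 1. Record at baseline the time since the last stroke or TIA, or that there was none.
2. Stratify the random list by recent event versus chronic or no event, with the cut-off chosen by the investigators before recruitment begins.
3. Replace the unadjusted t test on MoCA change with a linear model containing treatment and this factor.

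Steps 2 and 3 belong together. Stratifying the list alone removes the imbalance (0.09 of the 0.45 in the example at f = 0.5, g = 3), but the unadjusted t test would still compute its standard error from about 0.45 instead of 0.36. With the factor in the model, and if the two classes capture the difference, the residual SD returns to about 3 and power to about 80%.

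The cost is one baseline item, a stratified list and one model term (97 instead of 98 residual degrees of freedom at 100 patients). No patient is excluded. The gain will be small if recent cases are few or recover little. Whether to restrict entry by interval is a clinical choice for the investigators, and this point does not ask for it.

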#### Exclusion criteria

Patients who (1) have a Mini-mental State Examination score < 21; (2) have co-morbidity including AD, Parkinson’s disease, frontotemporal dementia, or Huntington’s disease, central nervous system inflammatory demyelinating disease, epilepsy, psychosis, liver or kidney dysfunction, hypothyroidism, alcoholic or drug abuse related encephalopathy, depression; and (3) have severe visual impairment, hearing impairment, severe aphasia or limb dysfunction which might affect pre-assessment, will be excluded from the study.

#### Dropout criteria

Patients who (1) have poor clinical compliance (2) quit the RCT voluntarily will be considered as having dropped out.

In this procedure, we used the formula for calculating the sample size of two sample rates for disordered classified data. Taking the results of previous research with a similar study design of acupuncture arm [15] (RR = 80%, OR = 15%) into consideration, a sample size of 100 patients (50 for each group) should be recruited. Allowing 20% attrition, the recruited sample size for this RCT will be of 120 patients (60 in each group).

Upon fulfillment of selection criteria, 120 eligible participants will be randomly allocated into the intervention and control groups in a 1:1 allocation ratio. Randomization will be performed according to a random list of numbers generated by the randomization center of Shanghai University of Traditional Chinese Medicine. An independent researcher, who contacts no participant and is not involved in the data collection or analysis, will take charge of the participant allocation based on the mentioned random list as well as on the allocation sequence concealment.

All participants will receive moderate financial subsidies to cover the travel expenses and should stick to the schedule for all treatments and assessments as much as possible. Those who are unable to visit the clinic at the time of reservation should inform the instructor by phone in advance to reschedule.

Patients will receive their intervention in a personal space separated by screens and no communication between them will be allowed. Treatment will be conducted in 8 consecutive weeks, at a frequency of three sessions per week in both intervention and control groups, and all manipulation should be consistent with the standards of the Revised Standards for Reporting Interventions in Clinical Trials of Acupuncture (STRICTA) [16]. In both groups, a 30 × 60-cm plastic plate with a notch will be applied on the patient’s chest as a visual barrier. In each session, after skin sterilization with alcohol wipes, the licensed and experienced acupuncturists will apply, with or without needle insertion, 0.25 × 25-mm needles to acupoints DU20, EX-HN3, DU24, DU26, and EX-HN1 and 0.30 × 40-mm needles for acupoints DU17, HT7, PC6, GB20, and SP6. A 2 × 2-cm piece of tape will be used to affix each needle to the skin of the chosen acupoints. The needles at DU20 and EX-HN3 will be connected to a G6805-2 Multi-Purpose Health Device (Shanghai Medical Instruments High-Techno, China) with electrode clamps. It will be implied to all patients that the sensation they are experiencing is the real acupuncture sensation. After a 30-min retention period, all needles and tape will be removed.

The intervention group will have a real tube-needle insertion applied with disposable stainless steel needles (Wuxi Jiajian Medical Material Co., Ltd., Wuxi, China). In the sitting position, DU17 will be punctured obliquely towards jaw to a depth of 0.5 cun into the skin. After that, in the supine position, DU20 (with the needle tip pointing towards the ground), EX-HN3, DU24, DU26, EX-HN1, and GB20 (with the needle tip pointing towards the feet) will be punctured obliquely to a depth of 0.5 cun, while HT7 and SP6 (with the needle tip pointing towards the limb extremities) will be punctured perpendicularly to the respective depth of 0.5 cun and 1–1.5 cun. Appropriate needle manipulation (including lifting, thrusting, and rotating) will be applied for 10 seconds on each point so that the needling sensation (De-qi sensation) can be accomplished at each point.

The control group will undergo treatment with a special sham acupuncture device with a blunt-tip needle. This type of needle can provoke a needling sensation quite similar to real acupuncture as soon as it touches the skin, without insertion. The acupuncturists should pretend to do the needle manipulation for 10 seconds on each point as well. Similarly, the needles on DU20 and EX-HN3 will be connected to a G6805-2 Multi-Purpose Health Device, with the device switched off, and will remain in place for the next 30 minutes.

The details of interventions are elaborated on Table 1.

**Table 1 Tab1:** Details of intervention

	Intervention group	Control group
Acupoints	DU20, EX-HN3, DU24, DU26, EX-HN1, DU17, HT7, PC6, GB20, SP6	DU20, EX-HN3, DU24, DU26, EX-HN1, DU17, HT7, PC6, GB20, SP6
Depth of insertion	DU20, DU17, EX-HN3, DU24, DU26, EX-HN1, GB20, HT7; 10 mm SP6; 15 mm	No insertion
Needle type	Steel needles (Wuxi Jiajian Medical Material Co., Ltd., Wuxi, China)	Blunt-tip needle (Streitberger Placebo-needle)
Needle sensation	With de-qi sensation	Without de-qi sensation
Electric stimulation	Needles on DU20 and EX-HN3 connected to G6805-2 Multi-Purpose Health Device (Shanghai Medical Instruments High-Techno, China), with electric pulse at a frequency of 2.5 Hz and an intensity of 45 mA	Needles on DU20 and EX-HN3 connected to G6805-2 Multi-Purpose Health Device (Shanghai Medical Instruments High-Techno, China), without electric pulse
Frequency and duration	Three sessions per week for 8 weeks	Three sessions per week for 8 weeks

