### Data analysis

All original data will be entered and stored with Microsoft Excel 2010, while data from cases without baseline evaluation or follow-up will be excluded from the full analysis set, and analyses will be performed with SPSS version 23.0 software. In the statistical analysis, measurement data will be analyzed with the Student’s *t* test, ranked data with the rank sum test, and categorical data with χ^2^ test. Data will be expressed as mean ± standard deviation or median (first quartile, third quartile). All reported *P* values will be two-sided with confidence intervals at the 95% level, and a *P* value of less than 0.05 will be considered statistically significant.

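### Recruiting 120 patients with 20% attrition leaves 96, not the 100 the sample-size paragraph calls for

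*Protocol article*

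**What the plan says.** All the figures are in the sample-size paragraphs of the protocol article, which sit under Dropout criteria.

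- The calculation concludes that "a sample size of 100 patients (50 for each group) should be recruited".
- The next sentence adds the allowance for losses: "Allowing 20% attrition, the recruited sample size for this RCT will be of 120 patients (60 in each group".
- The randomisation paragraph adopts that number: "120 eligible participants will be randomly allocated into the intervention and control groups in a 1:1 allocation ratio". The Abstract also gives 120, 60 per group.
- Data analysis says what happens to patients who are not followed: "data from cases without baseline evaluation or follow-up will be excluded from the full analysis set".

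Nothing in the article defines attrition as a share of the 100, or explains the 120 in any other way.

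**The concern.** An attrition allowance should leave the required number in the analysis after the assumed fraction of recruited patients has been lost. Here the allowance appears to have been added as 20% of the target instead of being taken as 20% of the recruits. If so, the trial falls short of its own required number under its own attrition assumption. The full analysis set drops cases that lack follow-up, so such losses reduce the number in the MoCA comparison. At stake are a few patients and a small loss of power, together with a headline design figure that is wrong as stated.

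**Working it through.** **Inputs** (protocol article, Dropout criteria): required number n = 100 (50 per group); attrition d = 20%; recruited number N = 120 (60 per group); 1:1 allocation.

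**Step 1. Reproduce the stated 120.**
- n × (1 + d) = 100 × 1.20 = 120. Per group, 50 × 1.20 = 60. This matches exactly.
- n / (1 − d) = 100 / 0.80 = 125. Per group, 50 / 0.80 = 62.5, rounded up to 63, so 126 in total with equal arms. This does not match.

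The 120 therefore comes from multiplying by 1.2.

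**Step 2. What 120 delivers at the stated attrition.**

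| Recruited | Remaining after 20% loss | Against 100 |
|---|---|---|
| 120 (60 per group) | 120 × 0.8 = 96 (48 per group) | 4 short |
| 126 (63 per group) | 126 × 0.8 = 100.8 (50.4 per group) | met |

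**Step 3. The attrition that 120 covers.** 1 − 100/120 = 16.7%, that is, 20 losses. At 20% there would be 0.20 × 120 = 24.

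**Step 4. Effect on power.** The article gives no power for the 100, so this step is conditional. Data analysis fixes a two-sided test in which "a *P* value of less than 0.05 will be considered statistically significant". Suppose 50 per group gave 80% or 90% power. By the normal approximation, power at 48 per group is Φ[(1.960 + z) × √(48/50) − 1.960], with √(48/50) = 0.980:
- 80% (z = 0.842): 2.802 × 0.980 − 1.960 = 0.785, so power is 78.4% (78.3% by the t test).
- 90% (z = 1.282): 3.242 × 0.980 − 1.960 = 1.216, so power is 88.8% (88.8% by the t test).

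The sample size was derived from a formula for two rates, with inputs RR = 80% and OR = 15% that the article does not define. Two readings show the range:
- *A risk ratio of 0.80 and an odds ratio of 0.15 taken together.* These imply rates of 95.6% and 76.5% (0.765/0.956 = 0.80). Power with pooled variance is 79.7% at 50 per group and 78.0% at 48. With the unpooled formula, 48 per group still gives 80.2%.
- *Rates of 80% and 15%.* Power is essentially 100% at either size.

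The loss therefore runs from nothing to about 2 percentage points.

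**The case against.** The case on the other side has four parts.

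1. *The 20% could mean over-recruitment relative to the 100.* On that reading 120 is simply correct. But the sentence speaks of attrition, and the dropouts the article describes are enrolled patients who comply poorly or quit. Nothing in the text supports the alternative base.

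2. *Not every dropout is lost from the analysis.* This stands in part. Poor compliance counts as dropout, yet the full analysis set excludes only cases lacking a baseline evaluation or follow-up. A poorly compliant patient who was assessed could still be analysed. Nor does the article say whether follow-up there means any assessment after baseline or the later visits. So 96 is the analysed number only if all 24 dropouts lack the required data. For 100 to be analysed, at least 4 of the 24 would have to be assessed. The article does not claim this, and its allowance treats the whole 20% as lost.

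3. *The 100 is itself unverified.* This stands, but it is a separate matter. With no stated power and undefined effect inputs, the base cannot be checked, and the power figures above depend on assumptions. Whatever its origin, the step from 100 to 120 is wrong for 20% attrition. The article also says that 100 should be recruited and does not call it an evaluable number. The following sentence makes 120 the recruited number, so 100 can only be the figure before attrition.

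4. *The effect is trivial.* It is small, and the remedy should be equally small. That does not make the stated figures agree.

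**Conclusion.** The concern holds. The stated 100, 20% and 120 are inconsistent: 120 recruits leave 96 (48 per group) at 20% attrition and cover at most 16.7%. The shortfall of 4 patients is exact if attrition is a fraction of those recruited and dropouts are not analysed. The power loss, about 1 to 2 points from an assumed 80% or 90%, is not exact, because the article states no power and does not define its effect inputs. This is a correctable misstatement of what the design delivers and does not threaten the trial's validity.

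**What to change.** Keep 120 and correct the sentence in one of two ways.

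- **Preferred:** state that recruiting 120 patients (60 per group) leaves 96 (48 per group) if 20% are lost, and give the power or detectable difference for 96.
- **Minimum:** state that 120 patients allow for attrition of up to 16.7% while retaining 100.

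The minimum version costs one sentence. The preferred version costs somewhat more, because giving a power for 96 requires the planned power and the effect inputs behind the 100 to be stated. In both cases the stated figure becomes slightly less favourable, no extra patients are recruited, and the 120 in the Abstract and the randomisation paragraph stays as it is. If the sponsor prefers to keep both the 100 and the 20%, the recruited number becomes 126 (63 per group), 6 more patients, and the 120 must be changed wherever it appears.
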